### Outcomes

**Primary outcome:** The primary outcome will be the proportion of consulting adult patients intervened (screened and advice given to screen positives), calculated as the number of AUDIT-C positive patients that received oral advice or referral for advice to another provider in or outside the PHCU, divided by the total number of adult consultations of the participating providers per provider and per PHCU.

**Secondary outcomes:**
**-** 
**Screening and advice:** The proportion of patients screened will be calculated as the number of completed screens divided by the total number of consultations of all patients eligible for screening (as defined above) per participating provider, and averaged per participating PHCU. The proportion of patients advised will be calculated as the number of brief interventions delivered (received oral brief advice, and/or were given an advice leaflet, and/or were referred to another provider in or outside the practice), divided by the total number of screen positives per participating provider and averaged per participating PHCU. Information will also be collected on the number of screen negatives who received brief advice.**-** 
**Provider attitudes and provider alcohol health literacy:** Attitudes of the participating providers will be measured by the short version of the Alcohol and Alcohol Problems Perception questionnaire, SAAPPQ
^25,
135–
137^. The responses will be summed within the two scales of role security and therapeutic commitment. Individual missing values for any of the items in a domain will be assigned the mean value of the remaining items of the domain before summation. Provider alcohol health literacy will be assessed through knowledge of risks due to drinking
^123^, and reported descriptive and injunctive social norms of drinking
^124^.**-** 
**Patient alcohol health literacy and injunctive social norms:** the tally sheets include one question about alcohol being a cause of high blood pressure, liver problems, depression or cancer, as a simple measure of alcohol health literacy (knowledge part)
^123^; and, two questions about injunctive social norms of drinking alcohol
^124^. We will analyze changes over time from baseline to the end of the 18-month implementation period, comparing changes in the screened population of alcohol health literacy and injunctive social norms between intervention and control cities.

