### Participants

Approximately ten PHCUs per intervention and comparator cities will be involved, 60 PHCUs in total. The exact number of PHCUs will depend on the average number of registered patients per PHCU. In each city, the total number of recruited PHCUs should cover a population of about 80,000 registered patients (including children and adults). In jurisdictions, where PHC physicians work as individual practitioners, a PHCU can be defined for the purposes of the study as a virtual or physical location where three or more PHC physicians work. Identification of PHCUs who agree to participate in the studies will be drawn from administrative or academic registries of PHCUs at national, regional, or city levels. The process of recruiting PHCU will be described in detail by each country. Within each PHCU, eligible providers will include any fully trained medical practitioner, nurse or practice assistant with a non-temporary employment contract, working in the PHCU and involved in medical and/or preventive care. These providers will sign an informed consent for their participation. Dependent on customary country practice, participating PHCUs will receive a study fee.

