### Sample size

Our power calculations are based on the following assumptions: at baseline, 2.5/1,000 consulting patients will be found to be screen positive (based on an AUDIT-C cut-off score of 8) and advised to reduce their alcohol consumption (data from ODHIN study; [name], personal communication). To detect an increase in the number to 5/1,000 (a doubling), with 80% power and a significance level of 5%, and assuming a design effect of ten PHCUs per three cities per group (scale-up and comparator), with an ICC for PHCUs across countries = 0.03 (data from ODHIN study; [name], personal communication), a conservative estimate of 30 PHCUs across three scale-up cities and 30 across three comparator cities, about ten per city will be needed
^150^, assuming an average PHCU size of about 8,000 patients with a monthly consultation rate of 1,200 adult patients per PHCU (data from ODHIN study; [name], personal communication).

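### The proportion advised is a per-provider ratio over few or no screen positives, so for a possibly substantial share of providers it is undefined or rests on one or two patients

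*Protocol article*

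**What the plan says.** In the protocol article, the paragraph on screening and advice under Secondary outcomes takes brief interventions delivered, "divided by the total number of screen positives per participating provider and averaged per participating PHCU". The denominator is thus each provider's own screen positives, and the PHCU value is a mean of provider ratios. A brief intervention there is oral advice or referral, "and/or were given an advice leaflet". The primary outcome has a narrower numerator, "the number of AUDIT-C positive patients that received oral advice or referral for advice to another provider", and divides by consultations.

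The Sample size section supplies the relevant rates: "at baseline, 2.5/1,000 consulting patients will be found to be screen positive (based on an AUDIT-C cut-off score of 8) and advised", to be doubled to 5/1,000, with a "monthly consultation rate of 1,200 adult patients per PHCU" and "with an ICC for PHCUs across countries = 0.03". The Data collection section sets the formal evaluation in three four-week periods.

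The Participants section counts doctors, nurses and practice assistants as eligible providers but gives no number per PHCU. The nearest figure applies only where physicians work individually; a PHCU may then be "a virtual or physical location where three or more PHC physicians work".

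**The concern.** A ratio per provider needs at least one screen positive for that provider. With an AUDIT-C cut-off of 8, positives are scarce on the protocol's own figures, so some providers will have 0/0 and many others will have a denominator of one or two. Nothing in the article says how an empty provider enters the PHCU mean. The last-value rule under Statistical measures covers drop-outs only, and the exact and zero-inflated methods there are set out for the primary outcome.

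Two consequences follow if the mean is taken over the defined ratios. A provider with one positive weighs as much as one with ten. And if the intervention raises screening, more providers in intervention cities will have a defined ratio, so the two arms are averaged over differently selected providers.

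**Working it through.** The article states no expected number of screen positives per provider, so there is no figure of its own to reproduce. The check builds one from its planning inputs.

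**Inputs from the Sample size section:** rate of patients screened positive and advised, p = 0.0025 or 0.005; 1,200 adult consultations per PHCU per month, taken here as a four-week period; ICC 0.03 for PHCUs.

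**Assumptions, not in the article:** k = 3 to 10 providers per PHCU sharing consultations equally; a = the share of screen positives who are advised, set at 1, 0.5 or 0.25. The second is needed because p counts advised positives, while the denominator at issue is all positives. A provider with positives but none advised scores a defined zero.

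**Step 1, per PHCU.** Expected advised positives: 1,200 × 0.0025 = 3 and 1,200 × 0.005 = 6.

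**Step 2, per provider.** Screen-positive rate r = p/a; consultations m = 1,200/k, so 400 for k = 3 and 120 for k = 10. With equal rates, P(no positive) = (1 − r)^m. For example, with a = 1 and k = 3, 0.9975^400 = 0.367 and 0.995^400 = 0.135.

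| Share of positives advised (a) | Providers (k) | Expected positives per provider, at 2.5 / 5 per 1,000 | No positive, at 2.5/1,000 | No positive, at 5/1,000 |
|---|---|---|---|---|
| 1 | 3 | 1.0 / 2.0 | 37% | 13% |
| 1 | 10 | 0.3 / 0.6 | 74% | 55% |
| 0.5 | 3 | 2.0 / 4.0 | 13% | 2% |
| 0.5 | 10 | 0.6 / 1.2 | 55% | 30% |
| 0.25 | 3 | 4.0 / 8.0 | 2% | 0% |
| 0.25 | 10 | 1.2 / 2.4 | 30% | 9% |

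**Step 3, clustering.** Let the rate vary between PHCUs as a beta distribution with ICC 0.03, with providers in a PHCU sharing its rate. The beta-binomial shares with no positive are then 81% and 66% (a = 1, k = 3), 88% and 78% (a = 1, k = 10), 66% and 43% (a = 0.5, k = 3), and 78% and 60% (a = 0.5, k = 10). The stated ICC belongs to PHCUs and is applied here to screen positives, so these figures show direction and rough size only.

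**Step 4, when the arms differ.** Each table row holds a fixed, so the doubling comes wholly from more positives found. If it came wholly from advising more of the same positives, r would not move. For example, 0.0025/0.5 = 0.005/1 = 0.005, so with three providers the undefined share is 13% in both arms.

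**Step 5, what pooling changes.** Summed within the PHCU with a = 1 and equal rates, the share of PHCUs with no positive is 0.9975^1200 = 5.0% and 0.995^1200 = 0.2%. With ICC 0.03 it is 74% and 55%. Over 30 PHCUs per arm, the expected number of positives is at least 30 × 3 = 90 and 30 × 6 = 180, so a count-based analysis is defined at arm level either way.

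**The case against.** The strongest reply is that the size is not established. A reader might infer that the outcome is undefined for a large, arm-dependent share of providers. The documents do not support that as a fact. The planning rate counts positives who were also advised, the advised share and the number of providers are not given, and with three providers and a quarter of positives advised the undefined share is about 2% and 0%. A difference between arms also requires an effect through screening. These points stand, and they are why the result is a range.

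It can also be said that handling of empty denominators is detail for an analysis plan, that this secondary outcome is not tied to the four-week windows (data are collected in every month of scale-up), and that the article mentions hierarchical regression for further analyses. The absence of a rule is indeed no finding in itself. But the article does fix a per-provider ratio followed by averaging, and that choice makes such a rule necessary and gives sparse ratios full weight.

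Pooling does not remove conditioning on being screen positive. That is correct, and the fix should say so.

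Finally, the leaflet category might be read as an error or as contradicting the primary outcome. It is neither. A secondary outcome may use a broader definition openly stated, and the article does not claim that this one decomposes the primary. The care pathway's leaflet for patients scoring below 8 carries a different label, so it does not settle the matter.

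**Conclusion.** The point holds as a weakness in how one secondary outcome is constructed. On the article's planning figures, the per-provider ratio has a small denominator and will be undefined for a share of providers that may be substantial: under equal rates and 3 to 10 providers, from 2% to 74% at 2.5/1,000 and from 0% to 55% at 5/1,000, depending mainly on the advised share and the number of providers. Clustering raises these figures. Selection that differs by arm is a risk conditional on the intervention raising screening, which its training component aims at. The primary outcome and the screening proportion divide by consultations and do not share the problem.

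**What to change.** Define the proportion advised from counts: screen-positive patients advised over screen positives, both summed within the PHCU. Analyse it with a binomial model with a PHCU random effect. Providers or PHCUs with no positives then contribute no ratio, and the others are weighted by the positives they have. State that the result remains conditional on being screen positive.

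Also report the proportion with the primary outcome's numerator (oral advice or referral, screen positives only) and show leaflet-only patients on a separate line. The screening proportion needs no change.

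The cost is a change of wording. The tally sheets already record the AUDIT-C score and the advice or treatment given to each patient. The downside is that the estimand becomes patient-weighted rather than provider-weighted, which should be stated openly.

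### The secondary proportion advised is built as a per-provider ratio over very few screen positives; it should be analysed from summed counts and read as a pathway measure

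*Protocol article*

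**What the plan says.** Under Secondary outcomes, the proportion advised has a broad numerator: patients who "received oral brief advice, and/or were given an advice leaflet, and/or were referred to another provider in or outside the practice". That count is "divided by the total number of screen positives per participating provider and averaged per participating PHCU". So a ratio is formed for each provider over that provider's own positives, and the ratios are then averaged within the unit.

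The primary outcome in the Outcomes section uses a different denominator: its count is "divided by the total number of adult consultations of the participating providers per provider and per PHCU".

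The Sample size section gives the planning counts: "at baseline, 2.5/1,000 consulting patients will be found to be screen positive (based on an AUDIT-C cut-off score of 8) and advised", "with a monthly consultation rate of 1,200 adult patients per PHCU", and a target of 5/1,000. The Participants section counts doctors, nurses and practice assistants as providers. It gives no average number per PHCU, only a minimum of three physicians where doctors practise individually. The Data collection section provides for data in every calendar month of the 18-month period, besides the four-week measurement windows.

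**The concern.** A per-provider ratio needs enough screen positives per provider to be defined and reasonably stable. At the planning rate there are only a handful per PHCU per window, and several providers share them. Averaging such ratios gives a provider with one positive the same weight as a provider with five.

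The denominator also depends on screening, which the training and municipal support are meant to increase. The number of providers with any positives, and possibly the kind of provider and patient who enters, can therefore differ between arms because of the intervention. This is the secondary outcome that separates advising from screening, so a reader will be inclined to take an arm difference as an effect on advising.

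**Working it through.** **Inputs from the Sample size section:** 1,200 adult patients per PHCU per month, taken as one four-week window; 2.5/1,000 screened positive and advised at baseline; 5/1,000 at target.

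**Assumptions, because the document gives no figure:** 3-10 providers per PHCU with equal load; 80-100% of screen positives advised; Poisson counts.

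**Step 1. Advised positives per PHCU per window.** 1,200 x 0.0025 = 3 at baseline; 1,200 x 0.005 = 6 at target. If 80% of positives are advised, screen positives number 3/0.8 = 3.75 and 6/0.8 = 7.5.

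**Step 2. Providers with no screen positive.** With k providers, P(0) = exp(-positives per PHCU / k).

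| k | Baseline, 100% advised | Baseline, 80% advised | Target, 100% advised | Target, 80% advised |
|---|---|---|---|---|
| 3 | 37% | 29% | 14% | 8% |
| 4 | 47% | 39% | 22% | 15% |
| 5 | 55% | 47% | 30% | 22% |
| 6 | 61% | 54% | 37% | 29% |
| 8 | 69% | 63% | 47% | 39% |
| 10 | 74% | 69% | 55% | 47% |

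The ranges are 29-74% at baseline and 8-55% at target. Uneven screening between providers would raise these shares.

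**Step 3. Thin denominators among the rest.** Take k = 5 and 80% advised. At baseline the mean is 3.75/5 = 0.75, so P(1) = 0.75 x exp(-0.75) = 0.354. Among providers with any positive, 0.354/0.528 = 67% have exactly one, and their ratio can only be 0 or 1. At target the mean is 1.5, and the share is 0.335/0.777 = 43%.

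**Step 4. The same counts summed per PHCU.** Taking 100% advised, exp(-3) = 5% of units are empty at baseline and exp(-6) = 0.2% at target. The per-provider step creates most of the sparsity.

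**Step 5. Two ways to treat an empty provider, with advising held at 0.8 for everyone.**
- Scored 0: the expected index is 0.8 x (1 - P(0)). For k = 5 it goes from 0.8 x 0.528 = 0.42 to 0.8 x 0.777 = 0.62. For k = 3 it goes from 0.57 to 0.73, and for k = 8 from 0.30 to 0.49. Advising has not changed.
- Dropped: the expected index stays at 0.80. In simulation with 3-8 providers per PHCU, the two-stage average has about 34-42% more arm-level variance than the pooled proportion.

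**Step 6. Does pooling deal with a change of mix?** The inputs here are invented, for illustration only. Keen providers (30%) have 2 positives each and advise 80%. Reluctant providers (70%) advise 50%, and their positives rise from 0.2 to 1.2.
- Provider average, empty providers dropped: providers with any positive are 0.3 x (1 - exp(-2)) = 0.259 keen and 0.7 x (1 - exp(-0.2)) = 0.127 reluctant, the latter rising to 0.7 x (1 - exp(-1.2)) = 0.489. The index goes from (0.259 x 0.8 + 0.127 x 0.5)/0.386 = 0.701 to (0.259 x 0.8 + 0.489 x 0.5)/0.748 = 0.604.
- Pooled: (0.48 + 0.07)/(0.60 + 0.14) = 0.743 falls to (0.48 + 0.42)/(0.60 + 0.84) = 0.625.

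Pooling does not remove this effect; in this example it moves slightly more.

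**The case against.** The best defence has four parts.

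**The share of empty providers is not in the document.** A reader might infer that about half of all providers will be empty. That needs roughly 4-6 providers per PHCU and the baseline rate, and the share falls at the target. The defence is right here: only the range, with its assumptions, can be reported. The plan to invite each provider's first six consecutive positives in month 3 might suggest that more positives are expected. However, six is a cap on invitations and not a planning count.

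**No passage scores an empty provider as 0.** Handling of a zero denominator is commonly left to the analysis plan, which is not shown. So the missing rule is no finding, and the rise in Step 5 is conditional on one possible rule. What remains is that the article itself fixes the ratio-then-average formula. That formula is inefficient even under the more favourable rule.

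**The fall in Step 6 uses inputs without a source, and there the share of positives advised really does drop.** That stands. The example shows only that a mix shift can move the measure while each provider's advising probability stays the same. It does not show that this is to be expected. That comparator units screen selectively is likewise not stated anywhere, and the care pathway foresees screening all adults.

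**The article makes no separate efficacy claim for this outcome.** It is listed beside the proportion screened, and the primary outcome divides by all consultations. Hierarchical regression with covariates is foreseen for further analyses. This limits the consequence, but the definition itself stays as written.

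**Conclusion.** The point holds as a modest, inexpensive improvement to one secondary outcome. At the protocol's planning rates, a per-provider ratio is undefined for a substantial share of providers in each window: 29-74% at baseline and 8-55% at target, given 3-10 providers per PHCU, 80-100% of positives advised, equal load and Poisson counts. Many of the other ratios rest on one or two patients. With constant advising and empty providers dropped there is no bias, but arm-level variance is about 34-42% higher than with pooling.

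A reader might infer that the outcome will rise or fall without any change in advising. The document does not support that as a general statement. A spurious rise requires empty providers to be scored 0, or a changed mix of providers or patients. The fall was shown only under illustrative inputs. Nor is summing the counts a full cure, because who enters the denominator can still shift with the intervention. The primary outcome does not share this weakness.

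**What to change.** - Define the outcome as advised screen positives divided by screen positives, from summed counts. Units or providers without positives contribute nothing; they are not scored zero.
- Analyse it at patient level with a random effect for PHCU and, where the data allow, for provider, adjusted for AUDIT-C score and sex, both already on the tally sheets.
- Use the monthly data of the 18-month period in addition to the two follow-up windows, so that the counts are less thin.
- Report it beside the proportion screened and the primary rate, and state that its denominator is affected by the intervention. Adjustment for score and sex covers recorded patient mix only, and pooling does not correct a shift in which providers or patients enter.

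The cost is analysis wording; no new data are needed. The downside is that the estimate becomes patient-weighted instead of provider-weighted and is read as a descriptive pathway measure, not as a separate test of advising.

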### Increasing PHC activity

Two systematic reviews
^42,
43^ and two multi-country studies
^41,
44,
45^ have demonstrated the possibility of increasing the proportion of patients screened, and screen-positive patients given advice by their PHC providers. The WHO Phase III four-country study on the identification and management of alcohol-related problems in primary care found that the odds ratios for the impact of training and support on increasing higher screening proportions (defined as 20% or more of eligible patients screened) was 2.2 (95% CI=1.3 to 3.1) and on increasing higher intervention proportions (defined as 10% or more of eligible patients screened and advice given to screen positives) was 2.8 (95% CI = 1.6 to 4.0), albeit from very low baseline levels
^45^. In the more recent five-country European ODHIN (Optimizing Delivery of Health Care Interventions) study, providing training and support to PHC providers increased the number of patients screened by 50%, and providing financial reimbursement to PHC providers increased the number of patients screened by 100%, also from low baseline levels of 6/100 consulting adult patients screened
^41^. Other evidence has suggested that the impact of financial incentives on screening and brief alcohol advice in England might have limited effects
^46^. Although incentivised practices recorded higher levels of activity than those not paid to deliver alcohol interventions, overall rates of delivery remained low.

Most work has been undertaken in high-income countries. Whilst there has been some work in low- and middle-income countries
^47^, including countries of Latin America
^48–
53^, there is an opportunity to fast-track scale-up research and practice in such countries.
^54^

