### Aim and objectives

Driven by implementation science
^70,
76–
83^, this three-country study aims to test the extent to which embedding PHC-based screening and brief advice activity within supportive municipal action leads to improved scale-up of more patients with heavy drinking receiving appropriate advice and treatment. The study has the following objectives:
1. To deliver a tailored package for improving prevention and early identification of heavy drinking, with advice and treatment for case positives that is scalable at municipal level in a wide range of middle- income countries;2. To set-up and implement the scalable package with key stakeholders in three case study cities (scalable units) from Colombia, Mexico and Peru;3. To test the scale-up of the package for its impact on provider delivery of early identification and management;4. To identify and document the facilitators and barriers, and the organizational and resource requirements for going to full-scale, including full economic analyses; and5. To present a validated framework and strategy for going to full-scale, embedding the package into routine policy and practice, taking into account aspects of stigmatization and equity, that can be replicated globally in the future throughout municipalities.

Our hypothesis is that, by embedding the primary health care action in a community and municipal setting with added support will lead to a greater proportion of patients screened and advised for heavy drinking than achieved hitherto in implementation studies that focused on providers alone.

Countries from Latin America are selected as this is a sub-region of the world in which alcohol jumps from ninth globally to the fourth most important risk factor for morbidity and premature death
^14^. The three specific middle-income countries are chosen to represent Central (Colombia and Mexico) and Andean (Peru) Latin America. The three countries have pre-existing collaboration between the authors, who have experience in the area
^48–
53^.

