### Data collection

Based on the validated methodology of the ODHIN project
^41,
122^, PHC providers will document activity by completing paper or electronic (depending on the ability to use existing electronic health records) anonymous tally sheets that record eligible patients’ (aged 18+ years) AUDIT-C scores, if administered, DSM-5 11-item and PHQ-9 scores, and the advice or treatment given to each patient. The tally sheets will record the age, sex, employment status, and educational level of the patient, the latter as one proxy measure of socio-economic status. The tally sheets will also include: two questions that capture previous experience of being asked about how much the patient drinks and of being advised to reduce the amount drunk to provide information for UN Sustainable Development Goal 3.5
^12^; one question about alcohol being a cause of high blood pressure, liver problems, depression or cancer, as a simple measure of alcohol health literacy (knowledge part)
^123^; and, two questions about injunctive social norms of drinking alcohol
^124^.

Data will be collected for each calendar month during the 18-month scale-up period. Formal evaluation will take place during three measurement periods: 4-week baseline period; 4-week assessment period during the 9
^th^ month of the 18-month scale-up period; and, 4-week assessment period at 18-months, the end of scale-up period. PHCUs will return data on the number of adult (aged 18+ years) consultations per provider for the four-week baseline assessment period, and for each of the 18 months of the scale-up period.

At baseline, PHC providers will provide data on their age, sex and profession (doctor, nurse, practice assistant etc.). At baseline, and at two time points during the 18-month scale-up period (month 4.5 and month 13.5), providers will provide data on their alcohol health literacy and on their attitudes to working with patients with heavy drinking. The alcohol health literacy instrument will assess knowledge of risks due to drinking
^123^, and descriptive and injunctive social norms
^124^. The attitudes instrument will be the shortened version of the Alcohol and Alcohol Problems Perception questionnaire
^125^.

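### The patient literacy and norms comparison is made among screened patients, a group the intervention is meant to change, and no patient-level adjustment is stated for it

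*Protocol article*

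**What the plan says.** The *Secondary outcomes* part of the protocol article sets three features of this comparison.

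- **Time span:** "We will analyze changes over time from baseline to the end of the 18-month implementation period".
- **Population and contrast:** "comparing changes in the screened population of alcohol health literacy and injunctive social norms between intervention and control cities".
- **Measures:** one knowledge question and two norm questions on the tally sheet.

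*Data collection* describes the tally sheets as anonymous and completed by providers. On patient characteristics it says: "The tally sheets will record the age, sex, employment status, and educational level of the patient".

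Screening is itself an outcome: "The proportion of patients screened will be calculated as the number of completed screens divided by the total number of consultations". The hypothesis in *Aim and objectives* is that the municipal approach "will lead to a greater proportion of patients screened and advised for heavy drinking" than earlier provider-only studies achieved. Under *Implementation strategies*, intervention units get training, ongoing support and city-level action. Control units get a summary card without instruction, plus record sheets and guidance on filling them in.

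Two places bear on adjustment. *Statistical measures* opens with the primary outcome and then plans further regression analyses with covariates. The characteristics it lists are those of the PHCU and the city, with baseline-period measurements as covariates. The *Discussion* mentions propensity score matching to control confounding, without naming its unit, its variables or the outcomes it serves.

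**The concern.** A difference in changes between two arms, built from repeated cross-sections, can be read as an effect on patients' knowledge only if the make-up of the sampled group stays stable or shifts equally in both arms. Here entry to the sample depends on being screened. If the programme works as hoped, screening widens mainly in the intervention cities, and the month-18 group there includes patients who would not have been screened at baseline.

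The article gives a reason to think that make-up can matter. Under *Tailoring PHC screening and advice package* it notes that, in Mexico, men drink more than women but attend primary care much less often.

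At stake is the reading of a secondary outcome. Better alcohol health literacy is the first component of the care pathway and the aim of the media campaigns. A shift in who is screened could look like a gain, or hide one, with no patient's knowledge having changed. The primary outcome does not share this problem, because its denominator is all adult consultations.

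**Working it through.** The article gives no sample size, effect size or power for this outcome, so there is no stated figure to reproduce. The check asks how large an artefact the design allows.

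**Inputs from the article**

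- Baseline screening in the cited five-country study: "also from low baseline levels of 6/100 consulting adult patients screened". So s0 = 6%.
- In the same study, "providing training and support to PHC providers increased the number of patients screened by 50" per cent. So s1 = 9%. The doubling reported there, s1 = 12%, came with financial reimbursement.
- The cited four-country study's threshold for higher screening: "defined as 20% or more of eligible patients screened". So s1 = 20% as an upper illustration.
- From *Sample size*: 30 PHCUs per arm, 1,200 adult consultations per PHCU per month, ICC 0.03. The ICC is given for the primary outcome and is only borrowed here.

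**Assumptions, not in the documents**

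- Newly reached patients differ in correct knowledge by d points from those already being screened.
- Those screened at the baseline level keep their knowledge.
- The control arm stays at 6% with the same mix.
- Baseline correct knowledge is 60% (needed only for the last step).

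**Step 1: formula.** The newly reached share of the end-point screened group is (s1 − s0)/s1 = 1 − s0/s1. With no true change in anyone, the apparent change is (1 − s0/s1) × d in the intervention arm and 0 in the control arm.

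**Step 2: numbers** (points, taking the sign of d)

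| Screening in intervention arm | Newly reached share | d = 5 | d = 10 | d = 15 | d = 20 |
|---|---|---|---|---|---|
| 6% to 9% | 1 − 6/9 = 33% | 1.7 | 3.3 | 5.0 | 6.7 |
| 6% to 12% | 1 − 6/12 = 50% | 2.5 | 5.0 | 7.5 | 10.0 |
| 6% to 20% | 1 − 6/20 = 70% | 3.5 | 7.0 | 10.5 | 14.0 |

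At d = 0 every entry is zero. If both arms expand equally with the same d, the artefact cancels.

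**Step 3: could it be visible?** A normal-approximation, two-sided 5% test of the difference in changes was used. Each arm-period proportion has variance p(1 − p)/(30m) × [1 + (m − 1) × 0.03], where m is 1,200 times the screened share. The four samples were treated as independent and city-level clustering was left out, so the results are rough.

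For 6% to 9% and d = 10 (newly reached knowing less):

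- Baseline, both arms, and control end-point: m = 72, design effect 1 + 71 × 0.03 = 3.13, variance 0.24/2,160 × 3.13 = 0.000348.
- Intervention end-point: m = 108, design effect 1 + 107 × 0.03 = 4.21, p = 0.567, variance 0.2456/3,240 × 4.21 = 0.000319.
- Standard error: √(3 × 0.000348 + 0.000319) = 0.037.
- Artefact 0.033, giving a rejection probability of about 15% with no true change.

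For the three screening scenarios in turn:

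| d | 6% to 9% | 6% to 12% | 6% to 20% |
|---|---|---|---|
| 5 | 7% | 10.5% | 16% |
| 10 | 15% | 28% | 48.5% |
| 20 | 44% | 78% | 97% |

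The nominal level is 5%. These figures show that the artefact need not be negligible. They do not estimate its size in this study.

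**The case against.** **The article does not say the comparison is unadjusted.** A reader might infer a raw comparison, but the sentence names a population, a span and a contrast, and no model. Regression with covariates and propensity score matching both appear elsewhere, and the choice of covariates for a secondary outcome is often left to an analysis plan. This objection stands against any claim that adjustment is ruled out. It does not remove the point. The population is stated, and the places that mention adjustment either list only PHCU and city characteristics in a paragraph that starts from the primary outcome, or give no unit or variables.

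**Recording may not be confined to screened patients.** *Data collection* has the sheets record AUDIT-C for eligible patients where it was administered, so sheets may also exist for unscreened patients. Literacy is also collected in the follow-up questionnaires of consenting screen-positive patients, although these serve quality control and are not an outcome. It would be wrong to say that the data come only from screened patients. The stated comparison is nevertheless limited to them.

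**Patients may be traceable through electronic records.** The *Discussion* anticipates linking AUDIT-C scores with consultations and hospitalisations. That would not give repeated literacy measurements on the same patients.

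**The role of this outcome can be overstated.** A reader might take it as the test of the media and literacy component. No section gives it that role. It is one of several secondary outcomes, beside a wide process evaluation.

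**Part of the remedy is already there.** The outcome is worded for the screened population, and the proportion screened is reported as its own outcome. This is correct, and it keeps the change small.

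**The magnitude rests on an assumed gap.** This stands fully. The control mix may also move, since control units receive a screening card and record sheets.

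**Conclusion.** The point holds in a limited form. As written, patient literacy and norms are compared over time between anonymous cross-sections of screened patients. That group is defined by a post-baseline event which the intervention aims to increase, and no patient-level adjustment is stated for this outcome. A between-arm difference in changes could therefore partly reflect who was screened.

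The documents do not allow the size or sign to be derived. Given a stable control mix and unchanged knowledge among those already screened, the artefact is a third of d at a 50% rise in screening and half of d at a doubling. The value of d is unknown and may be zero or of either sign, so the bias could mimic a benefit, hide one or be absent.

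This is a worthwhile, inexpensive improvement to one secondary outcome. It is not a threat to the primary analysis.

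**What to change.** In *Secondary outcomes*, under patient alcohol health literacy and injunctive social norms, add text to this effect:

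> Changes will be compared between city types with adjustment for patient age, sex, educational level and employment status, or after standardisation on these variables to a fixed reference population, allowing for clustering by PHCU and city. The proportion of consultations screened and the make-up of the screened group will be shown by arm and measurement period beside the estimates. Results apply to screened patients. Selection on characteristics not recorded may remain.

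The reference population should be named in advance, for example the pooled baseline screened patients of both city types. If tally sheets are in fact completed for unscreened adults, consulting adults could serve instead.

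**Cost:** wording and a little analysis work, since all four variables are already on the tally sheet. Two limits should be stated. The four variables do not capture selection through suspected drinking, reason for visit or willingness to answer, so the remedy is partial. With three cities per arm, city-level variation can be estimated only crudely.
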